**LIST OF ABBREVIATIONS AND RELEVANT DEFINITIONS**

| **ABR** | **ABR form, General Assessment and Registration form, is the application form that is required for submission to the accredited Ethics Committee (In Dutch, ABR = Algemene Beoordeling en Registratie)** |
| --- | --- |
| **AE** | **Adverse Event** |
| **AR**  **AUC** | **Adverse Reaction**  **Area under the curve** |
| **CA** | **Competent Authority** |
| **CCMO** | **Central Committee on Research Involving Human Subjects; in Dutch: Centrale Commissie Mensgebonden Onderzoek** |
| **CTG** | **cardiotocografie** |
| **CV** | **Curriculum Vitae** |
| **DSMB** | **Data Safety Monitoring Board** |
| **EA Epidural analgesia** | **Epidural analgesia** |
| **EU** | **European Union** |
| **EudraCT** | **European drug regulatory affairs Clinical Trials** |
| **FBS** | **fetal blood sampling** |
| **GCP** | **Good Clinical Practice** |
| **HADS** | **Hospital Anxiety and Depression Scale** |
| **IB** | **Investigator’s Brochure** |
| **IC** | **Informed Consent** |
| **IM** | **Intra muscular** |
| **IMP** | **Investigational Medicinal Product** |
| **IMPD** | **Investigational Medicinal Product Dossier** |
| **IV** | **Intra venous** |
| **MAIN** | **Morbidity Assessment Index for Newborns** |
| **METC** | **Medical research ethics committee (MREC); in Dutch: medisch ethische toetsing commissie (METC)** |
| **NACS** | **Neurologic and Adaptive Capacity Scoring system** |
| **PCA** | **Patient Controlled Analgesia** |
| **RPCA** | **Remifentanil Patient Controlled Analgesia** |
| **(S)AE** | **(Serious) Adverse Event** |
| **SPC** | **Summary of Product Characteristics (in Dutch: officiële productinfomatie IB1-tekst)** |
| **Sponsor** | **The sponsor is the party that commissions the organisation or performance of the research, for example a pharmaceutical**  **company, academic hospital, scientific organisation or investigator. A party that provides funding for a study but does not commission it is not regarded as the sponsor, but referred to as a subsidising party.** |
| **SUSAR** | **Suspected Unexpected Serious Adverse Reaction** |
| **Wbp** | **Personal Data Protection Act (in Dutch: Wet Bescherming Persoonsgevens)** |
| **WDQ** | **Wijma Delivery Expectancy/Experience Questionnaire** |
| **WMO** | **Medical Research Involving Human Subjects Act (in Dutch: Wet Medisch-wetenschappelijk Onderzoek met Mensen** |
|  |  |

|  |  |
| --- | --- |

**SUMMARY**

**Rationale:** Epidural analgesia (EA) is considered to be the most effective method of pain relief during labor and is recommended as first method of pain relief by the Dutch Societies of Gynecologists and Anesthetists. In the Netherlands its uptake by pregnant women in labor of all ethnicities is still limited (10%), compared with other western countries (40-80%), mainly as a result of non-availability due to logistic problems.

**Objective**: To assess in women with a request for pain relief during labor the cost-effectiveness of remifentanil patient controlled analgesia (RPCA) as first choice compared to EA.

**Study design:** National multicenter randomized controlled trial (RCT), in 16 centers (university hospitals, teaching and non-teaching hospitals), in cooperation with midwifery practices.

**Study population:** Pregnant women, including low risk pregnant women under care of primary care midwives, will be offered to participate in the study. Only women who have been informed before active labor has started, will be eligible.

**Intervention:** Pregnant women with a request for pain relief during labor will be randomized before active labor has started to RPCA or EA.

**Main study parameters/endpoints:** The objective of this study is to test the hypothesis that remifentanil PCA is as effective as epidural analgesia with respect to pain appreciation scores. We will look at the following outcomes: costs, pain-appreciation, patient satisfaction, pain scores (pain-intensity), maternal and neonatal side effects.

**Analysis and sample size:** The initial analysis will be performed by intention to treat. We hypothesize that there is no difference in pain appreciation scores with the two sided test (alfa=0.05, power 1-beta=0.9). In this equivalence design in each group 102 women have to be treated to exclude a potential clinical relevant difference of 10% (10 point scale, estimated SD 2.2). After correction for cross-over and non-compliance 568 patients are required. When only 50 percent of all women need actually treatment 1136 women have to be randomized.

**Economical evaluation:** For both strategies the cost of perinatal care for mother and child of delivery and the next ten days after delivery will be registered and compared.

**Nature and extent of the burden and risks associated with participation, benefit and group relatedness:** In this study two already widely used methods of pain relief during labor will be compared. No experimental medication will be used. No additional physical examination is needed for this study, nor will extra blood be taken from the subjects. Already documented risk of remifentanil PCA are maternal respiratory depression, nausea/vomiting and itching. Known risks of epidural analgesia are hypotension, increased use of oxytocin and increased risk of instrumental delivery. Maternal side effects will be part of the study outcome. After delivery participating women will be asked to fill out a questionnaire.

# INTRODUCTION AND RATIONALE

EA is considered to be the most effective method of pain relief during labor and is recommended as first method of pain relief by the Dutch Societies of Gynecologists and Anesthetists (1). In the Netherlands its uptake by pregnant women in labor of all ethnicities is still limited (10%), compared with other western countries (40-80%), mainly as a result of non-availability due to logistic problems.

This is an undesirable situation, especially since the number of women asking for pain relief during labor is increasing.

Furthermore, at present in the Netherlands, pain relief during labor is of major interest and an important topic for pregnant women, health care providers and politicians, as is pointed out in a recent publication of the multidisciplinary board on issues in obstetric management installed by the Dutch government. One of their advices is that all Dutch women in labor should have access to adequate pain relief during labor. The working party of the Dutch guideline "Pain relief during labor" recommends using RPCA only in controlled setting and recommends a large trial. Nevertheless, over 1/3 of Dutch hospitals use RPCA on labor wards, probably because the presence of an anesthetist is not required.

A large amount of studies has been conducted on the subject of pharmacological methods of pain relief during labor, such as inhalation of nitrous oxide, parenteral injection of opioids and regional analgesia by epidural and combined spinal epidural. EA is considered to be the best form of pain relief (in reducing pain-intensity) during labor (2).

There are situations in which EA is contra-indicated, i.e. patients with coagulation disorders, a common problem in daily obstetrics in preeclampsia and HELLP syndrome, or patients with skeletal disorders. In these cases im or iv opioids provide an alternative. The most commonly used opioid is im pethidine. However, its analgesic effectiveness is widely challenged (3,4,5).

Recently a new opioid, remifentanil, was introduced. Remifentanil, is a new synthetic opioid (anilidopiperidine) with direct agonist action specifically on µ-opioid receptors (6). The rapid onset and offset of the drug make remifentanil very suitable for administration via patient controlled analgesia (PCA), which can be used for analgesia during labor. Placental transfer of remifentanil does occur but appears to be rapidly metabolized, redistributed, or both. There were no adverse neonatal or maternal effects, only mild maternal sedation and respiratory changes (7). There have been multiple clinical studies on the use of remifentanil in the parturient (8-20).

A recent randomized study that compared RPCA with EA showed that in terms of pain scores (pain-intensity), EA is superior to that provided by RPCA. However, there was no difference in the pain appreciation scores between the treatments (21).

These findings were confirmed in our own pilot study that compared pain and pain appreciation scores in 20 women, randomized for RPCA or EA.

In our unpublished data (pilot study and STER study), 100 women received RPCA and only in one case medication had to be stopped because of serious side-effects (decrease in respiratory rate).

We hypothesize that RPCA is as effective in improving pain appreciation scores as EA, with lower costs and easier achievement of 24 hours availability of pain relief for women in labor.

Since we know from other studies that equality in pain appreciation scores can be anticipated, this study will, next to pain appreciation, also investigate patient satisfaction and costs. In this study patients receiving PCA remifentanil will titrate themselves to an acceptable level of pain relief by pressing a button (and receiving an analgesic bolus dose).

Equi-analgesia or equi-efficacy among the treatment groups is an essential part of the study as it is the primary end-point of analgesic treatment during labor. The definition of equi-analgesia in our study is a difference in pain appreciation (VAS score) among the two study groups of 10% or less. Preliminary data in perioperative patients on PCA opioid treatment ([name], oral communication) indicate that at VAS scores ranging from 4 to 8 (the expected range in our study), changes (i.e. increases) in pain score of 10% or larger will prompt an action of the patient (i.e. she will require additional pain relief by pressing the PCA button). Extrapolating these data to the current study suggests that at VAS score differences of 10% or greater clinical differences in pain appreciation may be assumed.

It is expected that economical evaluation of both strategies will show a significant reduction in costs of this innovative strategy.

Other outcome measures are pain scores, patient satisfaction, maternal and neonatal outcome and validated questionnaires.

This study considering cost effectiveness of RPCA as first choice analgesia versus EA could strongly improve the care for 180.000 women, giving birth in the Netherlands yearly (according to LVR data (2008) 30% of pregnant women under care in a hospital need pain relief during labor), by giving them access to pain relief during labor if needed, 24 hours a day.

In the guidelines of gynecologist and midwives it is recommended to discuss the opportunities of pain relief during labor antenatal (1).

An estimation of costs for RPCA versus EA shows a decrease of 64 euro per patient. The difference in costs is due to the extra costs of anesthetic staff and nurses, required when EA is given. Nationwide this could potentially save 1.2-4.6 million euro per year, depending on the percentage of women needing pain relief, varying respectively from 10-40%.

The results of the study will provide insight on whether RPCA in women in labor will reduce costs as compared to EA, assuming RPCA is equivalent to EA with respect to pain appreciation scores. At present, no clinical study has been published or undertaken to investigate this issue.

This study will be a national multicenter RCT embedded within the Dutch Obstetric Consortium, in 16 centers (university hospitals, teaching and non-teaching hospitals) in cooperation with midwifery practices . Pregnant women will be randomized to RPCA or EA, before active labor has started and thereby will be informed on the assigned method of pain relief before labor starts (as in usual care). They will be only given pain relief during labor at their request or if a medical reason should arise.

Feasibility and compliance:

An ongoing study "Differences in maternal temperature and saturation after administration of remifentanil patient controlled analgesia (RCPA) or epidural analgesia (EA) during labor; STER study" in the Leiden University Medical Centre and in a recently published study on pain relief showed that randomization of women for the proposed methods of pain relief is feasible (22).

In the Netherlands, pain relief during labor is at present of major interest and an important topic for pregnant women, health care providers and politicians, as is pointed out in a recent publication of the multidisciplinary board on issues in obstetric management installed by the Dutch government. One of their advices is all Dutch women in labor should have access to

adequate pain relief during labor (23). Furthermore, the number of referrals to the hospital because of prolonged labor and request for pain relief in increasing, which will result in more women with a need of pain relief during labor. These developments will stimulate women to participate in studies on pain relief in labor.

We estimate that for proposed study for the inclusion of 1136 women in 27 months, at least 10 hospitals are needed. The collaborating hospitals have already 24 hours availability of epidural analgesia.

# OBJECTIVES

**Primary Objective:**

The objective of this study is to test the hypothesis that remifentanil PCA is as effective as epidural analgesia with respect to pain appreciation scores.

**Secondary Objectives:**

We will also look at the following outcomes:

- Overall score of satisfaction with pain after delivery
- pain scores
- maternal and neonatal side effects and outcome
- Costs

# STUDY DESIGN

Multicentre non-blinded randomized controlled clinical trial. Time schedule will be 36 months, 3 months for preparations, 27 months for inclusions and 6 months for data analysis and economic evaluations. The study will be embedded within the Dutch Obstetric Consortium, starting in 10 centers (university hospitals, teaching and non-teaching hospitals).

Counseling and obtaining informed consent of low risk pregnant women will be done by their own primary care midwives, supported by research nurses/midwives of the Dutch Obstetric Consortium.

# STUDY POPULATION

## Population (base)

Pregnant women who have been informed before active labor has started will be eligible.

Active stage of labor is defined as presence of regular, painful uterine contractions at

regular intervals of 2-3 minutes with cervical dilation.

## Inclusion criteria

- - - - Age >18 years
      - ASA physical status I or II

## Exclusion criteria

- Drug allergy: history of hypersensitivity to opioid or local anesthetic substances
- Contra-indication for epidural analgesia

During pregnancy, after randomization, the following are reason to withdraw the parturient from the study:

- Labor before 32 weeks or after 42 weeks of gestation
- Initial maternal SpO2 of less than 95%
- Initial maternal temperature of 38C or higher.
- Prior administration of regional of opioid analgesia (during this delivery within 6 hours before request pain relief)

Absolute contra-indications for epidural analgesia are fever with evidence of systemic infection, high intracranial pressure, use of anticoagulants (coumarine derivates, LMWH prophylactic dose <12 hours, therapeutic dose <24 hours), clotting disorders with longer bleeding time, thrombocytopenia (<80). It is possible that the anesthesiologist responsible for the epidural finds other contra-indications for epidural analgesia. This will be documented in the case report form.

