## Follow up of withdrawn subjects

Analysis will be done according to intention to treat.

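### Section 4.3 withdraws women from the study after open randomisation, which conflicts with the promised intention-to-treat analysis; at least one reason can depend on the arm

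*Protocol*

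**What the plan says.** Protocol section 4.3 (Exclusion criteria) has a list that applies after allocation: "the following are reason to withdraw the parturient from the study". The list has four entries:

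- "Labor before 32 weeks or after 42 weeks of gestation"
- an initial maternal oxygen saturation below 95%
- "Initial maternal temperature of 38C or higher"
- "Prior administration of regional of opioid analgesia (during this delivery within 6 hours before request pain relief")

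The word used is withdrawal from the study, not from the allocated method. No time point is given for the initial saturation or temperature.

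The Introduction says that women learn their assigned method before labour starts, and section 6.2 says that there is no blinding.

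Under the heading Follow up of withdrawn subjects, the protocol says only: "Analysis will be done according to intention to treat". Sections 4.4 and 8.1 also name intention to treat, and section 8.1 adds a per-protocol repeat. The primary outcome (sections 6.1.1 and 8.1) is the area under the pain appreciation curve from the start of active labour to its end, built from scores taken hourly and more often in the first hour of pain relief.

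**The concern.** Intention to treat needs outcome data on the women randomised. The primary outcome exists only if scores are taken while labour is in progress. If a woman leaves the study when one of the four reasons is met, her curve is missing or cut short, and no later analysis rule can recover it.

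The fourth reason matters most. Whether a woman has had a regional or opioid method earlier in the delivery is a decision made by her and her carers, who know which method she was allocated. The frequency of that decision, and the kind of woman it concerns, could differ between arms. The text also does not separate a woman who first received a method other than the allocated one (non-compliance, kept under intention to treat) from a woman with prior administration (withdrawn), so staff who know the allocation could class similar events either way.

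If the women lost differ by arm and differ in satisfaction, the estimated difference moves. In an equivalence trial a move towards zero can produce a false claim of equivalence, and a move away from zero can hide a true one.

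**Working it through.** **The plan's own figure.** Inputs from section 4.4: difference to exclude 10% of a 10-point scale = 1.0 point, SD 2.2, two-sided alpha 0.05, power 90%.

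- Per group: 2 × (1.960 + 1.282)² × 2.2² / 1.0² = 101.7, so 102.
- Cross-over and non-compliance of 10% and 30%: 102 / (1 − 0.10 − 0.30)² = 283.3, so 284 per group and 568 in total.
- Half need pain relief: 568 / 0.5 = 1136.

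All three figures reproduce. The chain allows for dilution and for women who need no analgesia. It has no term for post-randomisation withdrawal.

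**Shift from unequal withdrawal (illustration).** The protocol gives no withdrawal rates and no scores for withdrawn women, so both are assumed. If a share p of an arm is removed and those women score g points below that arm's mean, the mean of the rest rises by p × g / (1 − p). With g = 2:

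| Withdrawn, arm A v arm B | Rise in A | Rise in B | Shift in difference | Share of 1.0-point margin |
|---|---|---|---|---|
| 5% v 2% | 0.105 | 0.041 | 0.064 | 6% |
| 10% v 5% | 0.222 | 0.105 | 0.117 | 12% |
| 15% v 5% | 0.353 | 0.105 | 0.248 | 25% |
| 5% v 5% | 0.105 | 0.105 | 0 | 0% |

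**Effect on the error rate (illustration).** Suppose that withdrawal occurs in one arm only, that the women lost differ by 1 SD (2.2 points), that the true difference is exactly 1.0, and that the shift b is towards zero. Equivalence is declared when the 95% confidence interval lies within ±1.0. By normal approximation the chance of a false declaration is Φ(b/SE − 1.96), with SE = 2.2 × √(2/n) and n not reduced for the women lost. For n = 284, SE = 0.185.

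- No withdrawal: b = 0, chance 2.5%.
- 5%: b = 0.05 × 2.2 / 0.95 = 0.116, chance about 9%.
- 10%: b = 0.10 × 2.2 / 0.90 = 0.244, chance about 26%.

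For n = 102 the last two are about 6% and 12%. At 2% excess withdrawal, with gaps from 0.5 to 1.5 SD and either n, the chance is about 3% to 6%.

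**Loss of precision.** If losses are equal and unrelated to arm, only power suffers. At 5% loss it is 88.6%, and 1136 / 0.95 gives 1196 to randomise; at 10% it is 86.9%, and 1136 / 0.90 gives 1263.

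**The case against.** The protocol promises intention to treat under the very heading that deals with withdrawn subjects, and it never says that scoring stops. A reader might infer that the plan abandons intention to treat. The text does not support that. It leaves the two statements unreconciled.

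Three further inferences are tempting and do not hold.

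- **That all four reasons are open to influence.** Gestational age at labour can hardly depend on the allocated analgesic. Initial saturation and temperature are objective and read most naturally as checks before analgesia. If so, losses on them alike in both arms mainly cost precision.
- **That contra-indications found later remove women from the epidural arm.** Section 4.3 does say "It is possible that the anesthesiologist responsible for the epidural finds other contra-indications for epidural analgesia", but such findings are only to be recorded in the case report form and are not among the four withdrawal reasons. Section 6.3 makes the other method available, which is cross-over, and section 4.4 allows for cross-over.
- **That waiting for an anaesthetist would trigger the fourth reason.** The 6-hour window runs back from the request, and the wait comes after it. The Introduction also says that the collaborating hospitals already have epidurals around the clock.

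It can also be said that analysis sets belong in a statistical analysis plan, which is not shown. That is fair for the definition of the sets. It does not cover whether labour scores are still taken, which is a matter of conduct for the protocol to settle.

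Finally, every figure for the size of bias is assumed. That stands: no bias has been demonstrated.

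**Conclusion.** The point holds in a limited form. Section 4.3 takes women out of the study after open randomisation, the protocol elsewhere commits to analysing them by intention to treat, and nothing secures the scores which that analysis needs. At least one of the four reasons depends on care given with the allocation known, so the loss could be selective.

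The size is unknown. Under an assumed 2-point gap, the withdrawal rates tried shift the difference by 0.06 to 0.25 points, or 6% to 25% of the margin. The shift is zero if withdrawal and gap are the same in both arms, and small if withdrawal is rare. The direction cannot be predicted from the protocol. The effect of the lost numbers on power is minor by comparison. The passages should be reconciled before women are lost under the present wording.

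**What to change.** Reconcile section 4.3 with the section on withdrawn subjects.

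1. State that a woman who meets one of the four reasons after randomisation remains in data collection, for scores and for costs, and is analysed in her randomised arm in the intention-to-treat analysis.
2. Report the number meeting each reason by arm.
3. If any exclusion from the primary analysis is kept, limit it to criteria that allocation cannot affect, assessed at a defined time before analgesia and applied identically in both arms. Add a sensitivity analysis of all randomised women who have scores. This requires a time point for the initial saturation and temperature.
4. Women with prior opioid or regional analgesia may be left out of the per-protocol analysis, but not out of the intention-to-treat analysis.

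Which treatment these women receive is for the sponsor to settle and is not part of this point.

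The cost is protocol wording, plus scores for a small number of extra women on forms already in use. If all women are retained, 568 and 1136 need no change on this account.

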## Sample size calculation

The initial analysis will be performed by intention to treat. We hypothesize that there is no difference in pain appreciation scores with the two sided test, an alpha of 0.05 and 90% power. In this equivalence design in each group 102 women have to be treated to exclude a potential clinical relevant difference of 10% (10 point scale, estimated SD 2.2). Allowing for 10% and 30 % cross-over/ non-compliance in the control group and experimental group respectively, 568 patients are required. When only 50 percent of all women need actually treatment 1136 women have to be randomized. We estimate that in the group of pregnant women who are willing to participate in the study 50% will actually need pain relief. This in contrast to the general Dutch pregnant population, which is known for a low uptake of pain relief during labor.

**4.4.1** Sample size for population of low risk pregnant women.

We hypothesize that there is no difference in pain appreciation scores with the two sided test, an alpha of 0.05 and 90% power. In this equivalence design in each group 102 women have to be treated to exclude a potential clinical relevant difference of 10% (10 point scale, estimated SD 2.2).

We estimate that in the group of pregnant women who are willing to participate in the study 50% actually need pain relief. Therefore 408 women have to be randomized.

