  23. Apgar 1 and 5 minutes: continuous, quantitative
  24. Arterial umbilical cord pH: continuous, quantitative
  25. Admission to neonatal ward: categorical, quantitative (yes/no)
  26. Number of visits to/from primary health care mother: continuous, quantitative
  27. Number of visits to/from primary health care child: continuous, quantitative
  28. Number of visits to/from gynecologist: continuous, quantitative
  29. Number of visits to/from pediatrician: continuous, quantitative
  30. Duration of neonatal admission: continuous, quantitative

Duration of maternal admission: continuous, quantitative

We will report on the primary outcome measure, pain appreciation, as area under the pain appreciation curve (AUC), this as a measure for the aggregate effect of pain appreciation over a period of time (27). Total pain relief (TOTPAR) is a time weighted measure of AUC or total area under the pain appreciation curve and is a summary measure that integrates serial assessments of a subject’s pain appreciation over the duration of the study. The AUC will be analyzed from the start of active labor and for the whole duration of labor. We will also perform analysis from start of pain relief for the duration the pain relief is given. Subgroup analysis is planned for the AUC for 0-4 hours, 4-8 hours and >8 hours after the start of pain relief.

The trial is designed as an equivalence trial in which the null hypothesis

is that the difference in pain appreciation score between the two treatment groups is

greater than 10%. Preliminary data in perioperative patients on PCA opioid treatment show that changes (i.e. increases) in pain score of 10% or larger will prompt an action of the patient (i.e. she will require additional pain relief by pressing the PCA button). Extrapolating these data to the current study suggests that at VAS score differences of 10% or greater clinical differences in pain appreciation may be assumed.

The analysis of the randomised clinical trial will be by intention to treat, stratified for

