## Interim analysis

No interim analysis will be performed. Because of the suggested design of the trial where equivalence is expected all 1136 women have to be randomized in order to achieve sufficient power. Both remifentanil PCA and epidural analgesia are widely used in the Netherlands as pain relief during labour and no adverse events have been recorded to date.

Serious Adverse Events (SAEs) and Suspected Unexpected Serious Adverse Reactions (SUSARs) will be reported to a Data Safety Monitoring Committee (DSMC). The DSMC can order to perform an interim analysis and, if indicated, terminate the trial prematurely.

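### The 102 per group in 4.4 and 4.4.1 omits the equivalence split of beta; the low-risk trial then has about 80% or 89% power, depending on an unstated interval, not 90%

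*Protocol*

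**What the plan says.** Section 4.4 sets the error rates: "We hypothesize that there is no difference in pain appreciation scores with the two sided test, an alpha of 0.05 and 90% power". It then gives the number: "In this equivalence design in each group 102 women have to be treated to exclude a potential clinical relevant difference of 10"%, on a 10-point scale with an estimated SD of 2.2. The Summary repeats the same terms.

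Section 4.4 raises this figure for 10% and 30% cross-over or non-compliance to 568 treated women. It then doubles that to 1136 randomised, because half are expected to need pain relief. Section 4.4.1 repeats the 102 per group for low-risk women and applies only the 50% uptake, giving 408 randomised. Section 8.1 says that the low-risk women form a separate trial with its own analysis.

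Section 8.1 also states the hypothesis to be rejected: the null hypothesis "is that the difference in pain appreciation score between the two treatment groups is" greater than 10%. The only confidence level named in that section is 95%, for relative risks. No interval is named for the equivalence decision.

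**The concern.** A trial that aims to reject a null hypothesis of non-equivalence succeeds only if it rules out a difference beyond the margin in both directions. When the true difference is zero it can fail on either side, so the type II error has to be shared between the two sides. A calculation that puts all of beta on one side gives too small a number for the power claimed.

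This matters most where the bare figure is the final one, as in 4.4.1. An equivalence trial with less power than stated is more likely to end inconclusive even if the treatments are truly equal. Section 8.1 plans the separate low-risk analysis so that it will persuade primary as well as secondary care providers.

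**Working it through.** **Inputs**

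- Two-sided alpha 0.05 and power 90% (4.4, 4.4.1, Summary).
- SD 2.2, and a difference of 10% on a 10-point scale (4.4, 4.4.1). I read this as a margin of 1.0 point. The protocol does not state the margin in points, so this is an assumption; step 1 supports it.
- Equal groups: "in each group 102 women have to be treated".
- True difference zero, following section 1: "Since we know from other studies that equality in pain appreciation scores can be anticipated".

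**Step 1: reproduce the protocol's figure.** The formula for detecting a difference d with a two-sided test is n = 2 × (z₀.₉₇₅ + z₀.₉₀)² × SD² / d².

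2 × (1.960 + 1.2816)² × 2.2² / 1.0² = 101.7, rounded up to 102. The match is exact.

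**Step 2: the equivalence formula.** At zero true difference, n = 2 × (z₁₋ₐ + z₁₋β/₂)² × SD² / margin², so z₀.₉₅ = 1.645 replaces 1.2816. Here a is the one-sided level of each test.

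- 95% interval (a = 0.025): 2 × (1.960 + 1.645)² × 2.2² = 125.8, so 126 per group.
- 90% interval, two one-sided 5% tests (a = 0.05): 2 × (1.645 + 1.645)² × 2.2² = 104.8, so 105 per group.

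**Step 3: power at 102 per group.** SE = 2.2 × √(2/102) = 0.308, and margin / SE = 3.246. Power = 2Φ(margin/SE − z₁₋ₐ) − 1.

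- 95% interval: 2Φ(3.246 − 1.960) − 1 = 80.2%.
- 90% interval: 2Φ(3.246 − 1.645) − 1 = 89.1%.

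Using the t distribution gives 79.6% and 88.8%, with 127 and 106 needed.

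**Step 4: where the shortfall lands.**

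- *Low-risk trial (4.4.1):* 2 × 102 / 0.5 = 408. There is no other inflation, so step 3 applies in full. Keeping 90% power would take 4 × 126 = 504 randomised (95% interval) or 4 × 105 = 420 (90% interval).
- *Main trial (4.4):* 102 / (1 − 0.1 − 0.3)² = 283.3, so 284 per arm; 2 × 284 = 568, and 568 / 0.5 = 1136. With 284 per arm the power at zero true difference is 99.95% (95% interval) or 99.98% (90% interval). If only compliers count, about 0.9 × 284 ≈ 255 and 0.7 × 284 ≈ 199, it is still 99.6% under the 95% interval.

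**Step 5: sensitivity at 102 per group.**

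| Assumption | 95% interval | 90% interval |
|---|---|---|
| Margin 1.0, true difference 0 | 80% | 89% |
| Margin 1.0, true difference 0.2 | 71% | 82% |
| Margin 1.0, true difference 0.3 | 61% | 73% |
| Margin 0.9, true difference 0 | 66% | 80% |

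The last row is included because section 6.1.1 describes the scale as 1 to 10, a range of 9 points, while section 6.3 gives 0 to 10.

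**The case against.** The strongest reply is that 80% is not a fixed result. Two one-sided tests at 5% each are a standard equivalence rule, and nothing in the protocol excludes them. Under that rule 102 gives 89%, and three more women per group would reach 90%. This stands: a reader might infer a flat shortfall of ten points, but the documents support only a range from about one point to about ten. The 95% interval is the more natural reading of a two-sided test at alpha 0.05, and 1.96 is the value that reproduces 102, but neither fact settles the rule. An analysis plan that chose the 90% interval would shrink the gap without closing it.

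Second, the protocol names no formula. A non-inferiority calculation at one-sided 0.025 also gives 102, so the origin of the figure cannot be proved. What can be said is that it matches a calculation that leaves beta unsplit.

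Third, the main trial does not share the shortfall. A reader might infer that its power is also below 90%, or that section 8.2 is wrong in saying that "all 1136 women have to be randomized in order to achieve sufficient power". The documents do not support either: 284 treated per arm is well above what either rule needs at zero true difference. Whether the cross-over inflation suits an equivalence design is a separate question.

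**Conclusion.** The point holds, within limits. The 102 per group is presented as an equivalence number with 90% power, yet it equals the number for detecting a 1-point difference and falls short of 90% for equivalence under both usual decision rules. In the low-risk trial of 4.4.1 the power is about 80% with a 95% interval or about 89% with a 90% interval. Both are best cases: they assume a margin of 1.0 point, SD 2.2, no true difference, and 102 treated and analysed women per group. In the main trial the starting figure is derived in the same way, but the planned number of treated women more than covers it. There the defect is in the stated derivation, not in the nominal power.

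**What to change.** - State which confidence interval decides equivalence (95%, or 90% from two one-sided 5% tests), and give the margin in points on a single defined scale.
- Recompute the base number with the equivalence formula. With a 1.0-point margin and SD 2.2 this is 126 per group (95% interval) or 105 (90% interval).
- In 4.4.1, restate the power of 102 treated per group as about 80% (95% interval) or about 89% (90% interval), at best.
- In 4.4 and the Summary, quote the main trial's power from the 568 treated women by the same formula, with its assumptions.

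Enrolment need not change. The cost is a revised paragraph and a less favourable stated power for the low-risk trial.
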